**Table 4. Evaluation of best overall response**

| Target lesions
At 12 months | New Lesions at
treated site(s) | Overall response
at 24 months |
|--------------------------------|-----------------------------------|----------------------------------|
| CR                             | No                                | CR                               |
| PR                             | No                                | PR                               |
| SD                             | No                                | SD                               |
| PD                             | Yes or No                         | PD                               |
| CR                             | Yes                               | PD                               |

PR

Yes

PD

CR: complete response; PR: partial response; SD: stable disease; PD: progressive disease

- In some circumstances it may be difficult to distinguish residual disease from normal tissue. When the evaluation of complete response depends on this determination, it is recommended that the residual lesion be investigated (biopsy/Histology) to confirm the complete response status.

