#### **Efficacy analysis:**

Primary efficacy endpoint: Complete Response (CR).

The number of lesions treated per subject will be summarised.

The number (and percentage) of lesions in each category (CR, PR, SD and progressive PD) at each timepoint (6 months, 12 months and 24 months) and the overall best response will be presented. The percentage of lesions achieving CR during the study (i.e., CR being the best overall response) will be estimated and presented with exact 95% confidence limits overall and by tumour type.

Secondary efficacy endpoints: Change from baseline in QoL, comfort of treatment, and cosmetic outcomes.

The QoL questionnaire will be scored according to the author's instructions. Change from baseline in score will be calculated. Descriptive statistics will be presented for actual score and change from baseline by timepoint, and overall and by tumour type (BCC/SCC). A mixed model will be fitted with change from baseline as the outcome variable. Baseline score will be included as a covariate and timepoint (6 months/12 months) tumour type, tumour stage as factors. Other relevant prognostic factors assessed at baseline will be included. From the model the adjusted mean change at each timepoint will be obtained and presented with 95% confidence limits. Adjusted mean change will be estimated overall and by tumour type.

Comfort with treatment is being assessed using a questionnaire. The frequency (and percentage) of subjects reporting each option for each question will be presented.

Cosmetic outcome (subject and clinician rated) is being assessed at 12 months and 24 months using a visual analogue score (VAS). Descriptive statistics will be presented overall and by tumour type (BCC or SCC). A mixed model will be fitted with VAS as the outcome variable. Tumour type and tumour stage will be included as factors. Other relevant prognostic factors assessed at baseline will be included. From the model the adjusted mean score will be obtained and presented with 95% confidence limits. Adjusted mean score will be estimated overall and by tumour type.

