**24 month follow up visit:**

- Photography of treated lesions (medical photographer or site digital camera)
  - CTCAE grading. Grading can be found in protocol appendix 1
  - Cosmetic outcome; subject rated. To be completed on Trial app (or directly into the eCRF if subject does not have a smart phone). VAS image found in the protocol appendix 3
  - Cosmetic outcome: Clinician rated. To be completed into the eCRF using VAS in the protocol appendix 3
  - Modified Visual RECIST assessment. Guide to assessment is found in protocol appendix 5
- 
- Histology to be performed if lesion is visible, suspected or is the site's regular clinical practice
  - General review for wound complications and radiation changes. Radiation changes at months 24 are to be recorded as the CTCAE grading in protocol appendix 1, **excluding** Radiation dermatitis.

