## **11.7 Efficacy Analyses**

### **Primary efficacy endpoint: Complete Remission (CR)**

The number of lesions treated per subject will be summarised.

The number (and percentage) of lesions in each category (CR, partial response [PR], stable disease [SD] and progressive disease [PD]) at each timepoint, and the overall best response will be presented. The percentage of lesions achieving CR during the study (i.e., CR is the

best overall response) will be estimated and presented with exact 95% confidence limits overall and by tumour type.

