### Response Criteria

#### Evaluation of target lesions

- \* Complete Response (CR): Disappearance of all target lesions
- \* Partial Response (PR): At least a 30% decrease in the sum of the LD of target lesions, taking as reference the baseline sum LD
- \* Progressive Disease (PD): At least a 20% increase in the sum of the LD of target lesions, taking as reference the smallest sum LD recorded since the treatment started or the appearance of one or more new lesions
- \* Stable Disease (SD): Neither sufficient shrinkage to qualify for PR nor sufficient increase to qualify for PD, taking as reference the smallest sum LD since the treatment started

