#### Evaluation of best overall response

The best overall response is the best response recorded from the start of the treatment until the 24 month follow up (taking as reference for PD the smallest measurements recorded since the treatment).

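### Table 4 takes target status only at 12 months, so a lesion that clears between 12 and 24 months is non-CR in the table but CR under the definition above it

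*Protocol*

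**What the plan says.** Appendix 5 gives two rules for the same quantity.

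- In words: "The best overall response is the best response recorded from the start of the treatment until the 24 month follow up".
- In a table, headed "Table 4. Evaluation of best overall response", with the columns "Target lesions At 12 months | New Lesions at treated site(s) | Overall response at 24 months". With no new lesion, each 12-month category passes unchanged to the last column: CR to CR, PR to PR, SD to SD.

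The primary analysis depends on this quantity. The Synopsis (Efficacy analysis) states: "The percentage of lesions achieving CR during the study (i.e., CR being the best overall response) will be estimated". Section 11.7 says the same in nearly the same terms.

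The 24-month target measurement is planned. Section 9.1.3 lists, for that visit, "Modified Visual RECIST assessment. Guide to assessment is found in protocol appendix 5". Table 2 schedules the assessment, Table 5 has a 24-month column, and the Synopsis says that the categories "at each timepoint (6 months, 12 months and 24 months) and the overall best response will be presented".

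The progression rule in Appendix 5 can be met by growth of the target alone: "At least a 20% increase in the sum of the LD of target lesions, taking as reference the smallest sum LD recorded since the treatment". New lesions are the alternative route.

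**The concern.** Table 4 is the protocol's only table for deriving best overall response, and it has no place for the target lesion as seen at 24 months. An analyst who programs the table and one who programs the sentence above it will classify the same late-clearing lesion differently, and the difference lies on the boundary between CR and non-CR that defines the primary endpoint.

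The table also mixes two quantities. Its title names a best response over time; its last column names a status at 24 months. It delivers neither reliably.

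**Working it through.** **Inputs.** Table 4 and the response definitions (Appendix 5); n = 120, one lesion per subject, one-sided alpha 0.025, benchmark and assumed CR rates (Section 11.1, Table 3).

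**Step 1: the plan's own figure.** Exact binomial test: the pass mark r is the smallest number with P(X ≥ r | 120, benchmark) ≤ 0.025, and power is P(X ≥ r | 120, assumed rate).

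| Benchmark | Assumed rate | Pass mark r | Power | Exact lower 95% limit at r |
|---|---|---|---|---|
| 85% | 94% | 110 | 0.893 | 0.852 |
| 86% | 94% | 111 | 0.816 | 0.862 |
| 87% | 95% | 112 | 0.853 | 0.873 |
| 88% | 96% | 113 | 0.891 | 0.884 |
| 89% | 97% | 114 | 0.930 | 0.894 |
| 90% | 97% | 115 | 0.847 | 0.905 |

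All powers are at least 0.80, so the stated 120 reproduces. The sample size is not in question.

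**Step 2: table against text.** Rank CR above PR above SD above PD (progressive disease). With no new lesion and no PD at 12 months there are 3 × 4 = 12 combinations of 12- and 24-month target status. Table 4 returns the 12-month status; the text returns the better of the two. The cases that matter are:

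| 12 months | 24 months | Table 4 | Best response by the text | Status at 24 months |
|---|---|---|---|---|
| PR | CR | PR | **CR** | CR |
| SD | CR | SD | **CR** | CR |
| SD | PR | SD | **PR** | PR |
| PR | PD | PR | PR | **PD** |
| SD | PD | SD | SD | **PD** |

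As a best response, Table 4 disagrees with the text in 3 of 12 combinations (the first three rows). Two of them cross the CR boundary, and none involves regrowth. As a 24-month status, it is right only where nothing changes, 3 of 12, and differs in 9.

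**Step 3: the 6-month visit.** Table 4 ignores this as well. With CR, PR or SD at 6 and at 12 months and any status at 24 months there are 3 × 3 × 4 = 36 paths. Table and text differ on CR versus non-CR when the 12-month status is PR or SD (2 ways) and CR was seen at 6 or 24 months (12 − 2 × 3 = 6 ways): 2 × 6 = 12 paths. Four of these (2 × 2 × 1) arise from the 24-month status alone. These are counts of logical paths, not probabilities.

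**Step 4: size.** One lesion is 1/120 = 0.83 percentage points. At 111 and 112 CRs the exact lower limits are 0.862 and 0.873, so one lesion moves the limit by about 0.01. The lesions that could clear late are those not in CR at 12 months. At the lowest assumed rate that is 120 × (1 − 0.94) = 7.2, about 7; at the highest, 120 × (1 − 0.97) = 3.6, about 4.

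**The case against.** The strongest reply is that the governing text is clear. The Synopsis, Section 11.7 and the sentence above Table 4 all point to the best response during the study, and an analyst who follows them counts late clearance as CR. The table would then merely need aligning. That stands as a guide to the repair. It does not remove the conflict, because Table 4 carries the title of the quantity and gives another answer.

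A second reply is that few lesions are affected. Section 11.1 expects CR close to 100%, and under Sections 6.1, 7.3.1 and 9.1.4 subjects with PD or needing further treatment leave the study. This also stands: the figure of 7 is a ceiling. But nothing removes an untreated subject in PR or SD at 12 months.

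A third reply is that the Synopsis evaluation criteria and Section 9.2.1 speak of CR at 12 months, for which no 24-month input is needed. Sections 5.2 and 11.7 instead use CR during the study, and Table 4 labels its own output as 24 months, so this reading does not rescue the table.

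A reader might infer more than the documents support:

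- *The 24-month reading is thrown away.* It is missing from Table 4 only. It is scheduled, Table 5 assigns a category at each visit from that visit's own measurements, and nothing says that the by-visit percentages come from Table 4.
- *Regrowth corrupts the primary result.* PR, SD and PD are all non-CR, and a PR or SD lesion that later grows keeps PR or SD as its best response under the text too. Section 9.2.1 still withdraws subjects on PD.
- *The table omits SD with a new lesion.* No such row appears, but the table is visibly broken at that point in the copy read here, so its absence carries little weight. Appendix 5 already makes new lesions PD.

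**Conclusion.** Table 4 contradicts the definition of best overall response that it is meant to implement. The consequence for the primary endpoint is confined to target lesions not in CR at 12 months. Where such a lesion has disappeared at 24 months without a new lesion, the table gives PR or SD and the text gives CR.

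Following the table lowers the CR percentage, so the error is conservative for the sponsor's claim. It costs 0.83 points per lesion. If all of about 7 lesions cleared late, the total would be 7 × 0.83 = 5.8 points, but the documents give no rate of late clearance and the true number may be far smaller. These figures assume 120 analysed lesions, one per subject, and that the 94% of Table 3 is read as the 12-month rate; with more lesions each one weighs less. That one lesion equals one step in the pass marks of 110 to 115 shows only that the marks are consecutive whole numbers.

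Separately, the last column of Table 4 is mislabelled. A PR or SD target that grows at least 20% from its smallest recorded sum, with no new lesion, stays PR or SD there although it is PD at 24 months. This changes neither best overall response nor the CR percentage.

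**What to change.** Rewrite Table 4 so that its inputs are the target status at the visit being evaluated (6, 12 and 24 months) and new lesions at the treated site by that visit, and its output is the response category at that visit. Derive best overall response from these per-visit categories, in line with the sentence above the table, and state that this result feeds the primary CR percentage. Confirm that SD with a new lesion is covered, consistently with the progression rule in Appendix 5.

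The cost is one appendix table and its programming. No assessment or data item is added, because the 24-month measurement is already scheduled.

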#### Duration of stable disease

- SD is measured from the treatment until the criteria for disease progression are met (during the study period), taking as reference the smallest measurements recorded since the treatment started.

#### Response review

- Response is determined by the site PI

**Table 5. Example Modified Visual RECIST data collection:**

|                      | Location        | Baseline   | Follow up 6 months | Follow up 12 months | Follow up 24 months |
|----------------------|-----------------|------------|--------------------|---------------------|---------------------|
|                      |                 | Dimensions | Dimensions         | Dimensions          |                     |
| Target lesion 1      | inner right ear | 2.3x2.1    | 1.8x1.5            | 1.6x1.3             |                     |
| target lesion 2      | outer right ear | 2.4x1.2    | 2.0x0.9            | 1.5x0.7             |                     |
| Target lesion 3      |                 |            |                    |                     |                     |
| Sum Longest Diameter |                 | 4.7        | 3.8                | 3.1                 |                     |
| Response Rate %      |                 | N/A        | 19.1               | 34                  |                     |
| Response Category    |                 |            | Stable Disease     | Partial Response    |                     |

## Appendix 6. Guidance notes on Bleeding post treatment

Rhenium SCT is a non-invasive therapy. This poses an advantage over treatments such as surgery or taking medications. This also means that patients can continue other medications

they may be taking. Patients can take their previous medications in the usual way. This also applies to anticoagulants.

Now, due to the treatment itself, the Rhenium SCT has no influence on bleedings, neither directly nor indirectly. Nevertheless, three situations are conceivable during the treatment in which, theoretically, small superficial bleeding can occur.

The first possibility for a bleeding arises, when preparing for intervention. Scabs over the tumour need to be removed and even though this is not necessarily a traumatic procedure, the crusts can stick to the ground of the lesion. Loosening them can cause superficial bleeding.

The second situation where bleeding could theoretically occur, is when removing the foil. Small clots can be torn out by the adhesive film and cause the bleeding.

The third situation where bleeding could happen, is when the necrosis after some weeks is removed. If the crust / necrosis is still adhering to the substrate, abrupt removal of it can trigger local bleeding.

In all cases, purely local measures are required to stop the bleeding. The bleeding site should preferably be compressed mechanically until the bleeding stops. If this is not sufficient, the bleeding can be stopped with the help of fibrin glue.
